**11.6.2. Confidentiality**

Documented evidence that a potential investigator is aware and agrees to the confidential nature of the information related to the study must be obtained by means of a confidentiality agreement.

All information provided by GSK and all data and information generated by the site as part of the study (other than a subject's medical records) will be kept confidential by the investigator and other site staff. This information and data will not be used by the investigator or other site personnel for any purpose other than conducting the study. These restrictions do not apply to: (i) information which becomes publicly available through no fault of the investigator or site staff; (ii) information which it is necessary to disclose in confidence to an IEC or IRB solely for the evaluation of the study; (iii) information which it is necessary to disclose in order to provide appropriate medical care to a study subject; or (iv) study results which may be published as described in the next paragraph.

If the relevant CTA is inconsistent with this statement, that CTA's confidentiality provisions shall apply rather than the above statement.

**11.6.3. Publication**

Prior to submitting for publication, presentation, use for instructional purposes, or otherwise disclosing the study results generated by the site (collectively, a 'Publication'), the investigator shall provide GSK, MVI and Crucell with a copy of the proposed Publication and allow GSK, MVI and Crucell a period to review the proposed Publication (at least 60 working days prior to the Publication's submission). Proposed Publications shall not include either GSK's, MVI's or Crucell's confidential information.

At GSK's, MVI's or Crucell's request, the submission or other disclosure of a proposed Publication will be delayed for up to 90 days to allow those parties to seek patent or similar protection of any inventions, know-how or other intellectual or industrial property rights disclosed in the proposed Publication.

The publication provisions in the relevant CTA will supersede this statement.

**11.6.4. Provision of study results to investigators, posting to the clinical trials registers and publication**

Where required by applicable regulatory requirements, an investigator signatory will be identified for the approval of the clinical study report. The investigator will be provided reasonable access to statistical tables, figures, and relevant reports and will have the opportunity to review the complete study results at a GSK site or other mutually-agreeable location.

GSK will also provide the investigator with the full summary of the study results. The investigator is encouraged to share the summary results with the study subjects, as appropriate.

The results summary will be posted to the GSK Clinical Study Register at the time of the first regulatory approval or within 12 months of any decision to terminate development. In addition, a manuscript will be submitted to a peer-reviewed journal for publication within 12 months of the first approval or within 12 months of any decision to terminate development. When manuscript publication in a peer-reviewed journal is not feasible, further study information will be posted to the GSK Clinical Study Register to supplement the results summary.

## 12. COUNTRY SPECIFIC REQUIREMENTS

Not applicable.

**Appendix A      NHANES I cardiovascular risk criteria**

Using the Graziano, et. al. article, volunteers will be screened for cardiac risk factors and be given a screening electrocardiogram. The information will be recorded on a source document with the following noted:

Study ID # \_\_\_\_\_

**Risk factors**

Weight\_\_\_\_ kg

Blood pressure \_\_\_\_\_

Height\_\_\_\_\_

Smoker Y / N

Calculated BMI (kg/m^2)\_\_\_\_\_

Diabetes Y / N

**Using Table A (males) or Table B (females), 5-year cardiovascular risk:**

- ☐ Low
- ☐ Moderate
- ☐ High

**Electrocardiogram (EKG)**

12-lead EKG taken? Y / N

If not,  
reason \_\_\_\_\_

Electrocardiogram interpreted by

\_\_\_\_\_

Electrocardiogram interpretation

\_\_\_\_\_

Only volunteers with NHANES I low risk criteria as well as non-significant EKG, as determined by expert consultant cardiologist, are accepted in the study.

Table A (for Males)

[figure not shown]

Table B (for Females)

[figure not shown]

**Appendix B      Neurologic Examination Form****Cranial nerves**

Eye movements                      Normal/Abnormal

Tongue movements                  Normal/Abnormal

Facial expression                  Normal/Abnormal

**Muscle strength grading** (Normal: muscle can move in full range of motion, against full resistance. Abnormal: 0 Complete paralysis, no visible movement ; 1 Trace strength, some visible muscle contraction, with no movement of joint ; 2 poor strength, muscle can move the joint but not against gravity ; 3 Fair strength, muscle can move against gravity, but not against any examiner resistance ; 4 Good strength, muscle can move against moderate resistance, but not examiner full resistance).

Deltoid (non-dominant arm\* abduction at shoulder) Normal/Abnormal. If Abnormal: 0/1/2/3/4

Biceps (non-dominant arm\* flexion at elbow)                  Normal/Abnormal. If Abnormal: 0/1/2/3/4

Triceps (non-dominant arm\* extension at elbows)          Normal/Abnormal. If Abnormal: 0/1/2/3/4

Quadriceps (extension of the non-dominant\* knee)          Normal/Abnormal. If Abnormal: 0/1/2/3/4

Hamstrings (flexion of the non-dominant\* knee)              Normal/Abnormal. If Abnormal: 0/1/2/3/4

**Note: \*If the subject was vaccinated on the dominant side, then this assessment should be done on the dominant side and the information should be recorded on the eCRF accordingly. (Amended 09 June 2011)**

**Deep tendon reflexes grading** (normal will be from minimal to slightly hyperactive ; abnormal will be no response and hyperactive with clonus/tetany. Biceps (non-dominant\* elbow flexion)                      Normal/Abnormal. If abnormal : No response/Hyperactive with clonus, tetany

Patellar (non-dominant\* knee extension)                      Normal/Abnormal. If abnormal : No response/Hyperactive with clonus, tetany

**Note: \*If the subject was vaccinated on the dominant side, then this assessment should be done on the dominant side and the information should be recorded on the eCRF accordingly. (Amended 09 June 2011)**

**Sensitivity dermatome assessment: focus on the non-dominant arm**

C5 Upper-outer arm (deltoid/biceps region, avoiding the immediate vaccination surrounding region) Normal/Abnormal. If Abnormal: hypoesthesia/hyperesthesia/anesthesia/paresthesia

C6 Thumb side of lower arm, palm side of thumb and index finger Normal/Abnormal. If Abnormal hypoesthesia/hyperesthesia /anesthesia/paresthesia

C7 Middle finger (both sides) and dorsal side of hands and fingers Normal/Abnormal. If Abnormal: hypoesthesia/hyperesthesia/anesthesia/paresthesia

C8 palm side of ring and pinky fingers Normal/Abnormal. If Abnormal: hypoesthesia/hyperesthesia /anesthesia/paresthesia

T1 Medial aspect of lower and upper arms Normal/Abnormal. If Abnormal: hypoesthesia/hyperesthesia /anesthesia/paresthesia

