#### **5.4.2. Risks to the subjects and precautions to minimize risk**

##### **5.4.2.1. Risks associated with vaccination and mitigation of risks**

###### **Ad35.CS.01 vaccine**

As with many vaccines, the Ad35.CS.01 vaccine has shown mild to moderate injection site pain, swelling, or discomfort. There may also be some bruising or discoloring and rarely infection might occur. Other common side effects are fever, headaches, chills, nausea, vomiting, body aches, numbness or muscles weakness and tiredness. These reactions are usually greatest within the first 24-72 hours after vaccination and last 1-2 days. There is a rare possibility of an allergic reaction to the vaccine. As with any vaccine, unexpected serious adverse events, including allergic reactions to the vaccine components, may occur, although this has not been reported in prior studies with Ad35.CS.01.

In a previous study of consecutive administration of 3 doses of Ad35.CS.01 to various dose levels, some vaccinated individuals reported paresthesia and weakness in the vaccinated arm (refer to Section 1.1.2 for more details). The occurrence of new neurological symptoms after immunization will be monitored in this study in a standard way, using a standard neurological examination form assessing central and peripheral nervous systems, motor and sensory functions upon D0, D6 and D28 post first immunization ([Appendix B](#)).

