#### **5.4.3. Malaria Challenge**

Volunteers from both study groups completing their immunization course will be challenged with sporozoite-infected mosquitoes to determine whether the expected protective response has developed. Such challenges are mandated by the absence of any laboratory tests that will unequivocally predict protection. The challenge is scheduled to occur approximately 21 days (3 weeks) after the last vaccination visit (Study Day 77) and will be performed in a staggered fashion. The first 56 eligible subjects (28 subjects per study group) will be enrolled and vaccinated (Cohort A). Among the 56 vaccinated individuals a random selection of subjects eligible for challenge will be done according to the local SOP to ensure that a maximum of 46 vaccinated individuals (balanced by group) will progress to the challenge phase. The remaining subjects will not be challenged but will be followed for safety and immunogenicity up to 6 months after the last vaccination.

Unimmunized infectivity control volunteers will also be challenged to verify the adequacy of the challenge. The use of 4 to 6 unimmunized, malaria-naïve controls per challenge day is adequate since the procedure described has generally successfully infected such volunteers [Gordon, 1995]. The challenge of vaccinated subjects from Cohort A will be done at the WRAIR Insectary.

After safety and efficacy assessment for Cohort A, subjects from Cohort B and C (approximately 56 subjects per cohort) will be vaccinated. Of these subjects, a maximum of 46 vaccinated study participants per cohort will progress to the challenge phase. The challenge of Cohorts B and C will be conducted in parallel at WRAIR Insectary and the University of Maryland, CVD, respectively. Malaria-infected mosquitoes for challenge at the University of Maryland will be transported by WRAIR investigators to the insectaries at the University of Maryland for challenge of human subjects.

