- Unsolicited adverse events
  - a serious adverse event considered related to vaccination occurs in a study participant from the Ad35.CS.01 – RTS,S/AS01B – RTS,S/AS01B group
  - more than 25% of subjects from the Ad35.CS.01 – RTS,S/AS01B – RTS,S/AS01B group develop any Grade 3 unsolicited adverse event considered related to vaccination and persisting at Grade 3 for > 2 consecutive days.
- Standard neurological evaluation
  - more than 10% of subjects from the Ad35.CS.01 – RTS,S/AS01B – RTS,S/AS01B group develop abnormal neurological symptoms captured by standardized neurological evaluation ([Appendix B](#)).
- Laboratory adverse events
  - more than 25% of subjects from the Ad35.CS.01 – RTS,S/AS01B – RTS,S/AS01B group develop any Grade 3 laboratory adverse event considered related to vaccination.
  - more than 10% of subjects develop hematuria, not taking into account menstruating females if the hematuria coincides with their regular monthly time for their period or urinary tract infection.

If a holding rule has been met, vaccination of subjects in the subsequent cohort will only start if GSK, Crucell, MVI and investigators agree to it, following discussions with the SMC. All IRBs will be notified if a holding rule is activated or released after SMC review.

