#### 6.3.1. Injection technique

Intramuscular injections are administered in the deltoid of the non-dominant arm except for variances like tattoos, rashes, burns or other skin disorders subject to the discretion of the investigator when the dominant arm will be used for injection. **The buttock should not be used for administration of vaccines** because of the potential risk of injury to the sciatic nerve and the risk of decreased immunogenicity because of inadvertent subcutaneous injection or injection into deep fat tissue.

For all intramuscular injections, the needle should be long enough to reach the muscle mass and prevent vaccine from seeping into subcutaneous tissue, but not so long as to involve underlying nerves, blood vessels or bone. Vaccinators should be familiar with the anatomy of the area into which they are injecting vaccine. Although it is recommended to follow the guidelines provided below, an individual decision on needle size and site of injection must be made for each person on the basis of age, and the size of the muscle.

Intramuscular injections should be administered with caution to subjects with thrombocytopenia or a bleeding disorder since bleeding may occur following an intramuscular administration to these subjects. Firm pressure should be applied to the injection site (without rubbing) for at least two minutes.

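### The sensory section of the neurological form stays on the non-dominant arm even when the dominant arm was vaccinated, so paresthesia can be looked for in the wrong arm

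*Protocol*

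**What the plan says.** Section 5.4.2.1 gives the reason for the form. In an earlier study of Ad35.CS.01, "some vaccinated individuals reported paresthesia and weakness in the vaccinated arm". The present trial therefore monitors new neurological symptoms "using a standard neurological examination form assessing central and peripheral nervous systems, motor and sensory functions upon D0, D6 and D28 post first immunization".

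Injections normally go into the non-dominant deltoid. Section 6.3.1 allows exceptions for skin problems or tattoos, "subject to the discretion of the investigator when the dominant arm will be used for injection". Section 5.6.3.7 and the footnote to Table 22 allow the same exception.

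The form itself is in Appendix B. Under both muscle strength and deep tendon reflexes, the items carry an asterisk and the note added by Amendment 1: "If the subject was vaccinated on the dominant side, then this assessment should be done on the dominant side", with the eCRF entry made to match. The next section is headed "Sensitivity dermatome assessment: focus on the non-dominant arm". It has neither asterisk nor note. Its first item reads "C5 Upper-outer arm (deltoid/biceps region, avoiding the immediate vaccination surrounding region").

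Section 5.4.4.1.3 uses the results. Vaccination of the next cohort can be put on hold if more than 10% of ARR subjects "develop abnormal neurological symptoms captured by standardized neurological evaluation".

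**The concern.** Amendment 1 recognised that some subjects would be vaccinated in the dominant arm and that the examination should follow the injection. It made that correction for weakness but not for altered sensation. Both were reported earlier, and both were in the vaccinated arm. Paresthesia is a result option only in the sensory section, so the omission falls on the only part of the form able to record it.

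The form is completed on Days 0, 6 and 28 after the first dose, the only dose at which the ARR group receives Ad35.CS.01. Its results are tabulated by group for the Safety Monitoring Committee between doses (Section 5.4.4.1.2) and are what the neurological holding rule counts. If the unvaccinated arm is examined, a local sensory deficit is entered as normal and the count is too low.

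**Working it through.** **Which arm each section examines**

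| Part of Appendix B | Vaccinated in non-dominant arm | Vaccinated in dominant arm |
|---|---|---|
| Muscle strength | non-dominant (vaccinated) | dominant (vaccinated), by the note |
| Deep tendon reflexes | non-dominant (vaccinated) | dominant (vaccinated), by the note |
| Sensory dermatomes C5 to T1 | non-dominant (vaccinated) | non-dominant (**not** vaccinated) |

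The two notes cannot be read as covering the sensory section. Each refers to its own assessment and is tied by asterisk to the items above it. The note is repeated for the second section, which would be unnecessary if it carried forward. The record of changes in Appendix D shows edits to strength and reflexes only. The C5 item tells the examiner to keep clear of the injection site, which makes sense only if the vaccinated arm is being examined. For a subject vaccinated in the dominant arm, heading and item therefore disagree.

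**The holding rule in Cohort A**

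Section 5.4.3 gives the denominator: "The first 56 eligible subjects (28 subjects per study group) will be enrolled and vaccinated (Cohort A"). The threshold is 28 × 0.10 = 2.8, so the rule needs 3 subjects:

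- 2/28 = 7.1%, not met
- 3/28 = 10.7%, met

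One unrecorded subject can therefore change the outcome.

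**Subjects examined on the wrong side**

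The protocol gives no share of dominant-arm injections. Assuming 5% to 15%:

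- 28 × 0.05 = 1.4
- 28 × 0.15 = 4.2

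That is about 1 to 4 ARR subjects in Cohort A. These are subjects examined on the wrong side, not missed cases.

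**Missed cases**

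If 15% of ARR subjects have a detectable abnormality (also an assumption), and every abnormality is sensory only and missed whenever the dominant arm was vaccinated, the expected number missed is:

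- 28 × 0.15 × 0.05 = 0.21
- 28 × 0.15 × 0.15 = 0.63

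At that abnormality rate this is an upper bound, because an abnormality that also affects strength or reflexes would be caught on the correct side.

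**Effect on the chance of meeting the rule**

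Let p be the true rate of detectable abnormality and f the share of abnormal subjects missed. The number recorded is binomial with n = 28 and probability p(1 − f), and the rule is met at 3 or more. Both p and f are assumptions.

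| p | f = 0 | f = 5% | f = 10% | f = 20% |
|---|---|---|---|---|
| 10% | 0.541 | 0.505 | 0.468 | 0.391 |
| 15% | 0.813 | 0.783 | 0.749 | 0.670 |
| 20% | 0.939 | 0.922 | 0.902 | 0.848 |

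If the dominant-arm share is 5% to 15%, f cannot on average exceed that share unless dominant-arm subjects are more often affected. The 20% column therefore lies beyond the assumed range.

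**The case against.** The gap in the text is not in dispute. The case on the other side is that it matters little.

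- **Only exceptions are affected.** The non-dominant arm is the rule, and the true share of dominant-arm injections could be close to zero. This stands, and it is why every figure that depends on that share is conditional.
- **A sensible examiner would get it right.** The heading's wording is not exclusive, the C5 item points to the vaccinated arm, and the examiner has just moved two other tests to that side. This is plausible. But an examination meant to be standardized should not depend on the examiner departing from its heading, and the C5 item supports correcting the heading.
- **A missed case needs several things together:** dominant-arm injection, a sensory abnormality, no accompanying strength or reflex abnormality, and a literal reading of the form. This stands. Expected missed cases are well below the 1 to 4 subjects examined on the wrong side.
- **Other routes exist.** All adverse events are recorded from the first dose whatever their intensity, subjects are asked an open question, and there are visits on Days 1, 2, 3 and 6. Section 5.4.2.1 describes common reactions as usually greatest in the first 72 hours, before the Day 6 examination. A subject who complains of paresthesia would not go unseen. This limits the harm, but the neurological holding rule counts what the standardized evaluation captures, not spontaneous reports.
- **The hold is not automatic.** The committee may hold and the investigator may ask for a hold on any single event, so a count of 2 does not prevent action. True, but the committee would still be reading an understated table.

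**Conclusion.** The concern holds. For subjects vaccinated in the dominant arm, Appendix B directs strength and reflex testing to the vaccinated side and sensory testing to the other. Sensory testing is the only part of the form with paresthesia as a result. This is an instruction that is wrong for those subjects, and it conflicts with the form's own C5 item.

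The size is modest and rests on assumptions. At 5% to 15% dominant-arm injection, about 1 to 4 of the 28 ARR subjects in Cohort A have sensation examined on the wrong side. With a true abnormality rate of 15%, missing 10% of cases lowers the chance of meeting the holding rule from 0.813 to 0.749. If almost nobody is injected in the dominant arm, the effect is negligible. The efficacy analysis is not touched. It should be corrected because the rule turns on 3 subjects and the correction is very cheap.

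**What to change.** In Appendix B, mark the sensory heading with the same asterisk and place under it the note already used for strength and reflexes: when the dominant side was vaccinated, assess C5 to T1 on that side and record the side examined in the eCRF. This extends the sponsor's own Amendment 1 rule and introduces no new clinical rule.

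The cost is one line on the form and a side-examined entry for the sensory section in the eCRF. The existing notes call for the eCRF to be completed accordingly, but the protocol does not show whether a suitable field exists, so this should be checked. No visit, sample or analysis changes.

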**Cerebellar assessment:**

Finger to nose Normal/Abnormal

**Walk assessment:**

Normal/Abnormal

## Appendix C Laboratory assays

Any serum, plasma or blood cells not immediately used in immunological assays will be stored at -20°C or less for serum and in liquid nitrogen storage for blood cells, and would only be used to assess the immune response to vaccination or to malaria antigens, or to assess any potential toxicity of the vaccine. ***Serum for cytokine/chemokines analysis must be stored at -80°C or less. (Amended 09 June 2011)***

All assays will be performed in a blinded manner without regard to the investigational group assignment of the volunteer subjects.

### Hematological, biochemical and urine assays

Hematological testing (WBC, haemoglobin, and platelets), biochemical testing (ALT, AST and creatinine) and urinalysis (protein, blood) will be measured at regular intervals throughout the study period as listed in [Table 6](#).

Hematological, biochemical and urine testing will be performed at Quest or LabCorp laboratories using laboratory SOPs.

### Humoral immunity assays

Blood for analysis of humoral immune response will be obtained from each volunteer at timepoints indicated in [Table 6](#). After centrifugation, serum samples should be kept at – 20°C or less until shipment.

#### ***Antibody levels against CS (repeat region)***

Antibody levels against *P. falciparum* CS-repeat region will be measured at GSK Biologicals by standard ELISA methodology using plate adsorbed recombinant polypeptide R32LR antigen. Anti-CS antibody levels will be determined relative to a standard reference antibody as a control according to SOPs from the laboratory. Results will be reported in EU/ml.

#### ***Antibody levels against HBsAg***

Antibodies against hepatitis B surface antigen (HBsAg) will be measured at GSK Biologicals using an in-house validated ELISA assay. Results are expressed in mIU/ml and the cut-off for seroprotection is 10 mIU/ml.

#### ***Antibody levels against Ad35***

Neutralizing antibody titers against adenovirus type 35 will be determined using the validated neutralizing antibody assay at the GLP laboratory at Crucell [[Sprangers, 2003](#)]. This functional assay determines the anti-Ad35 neutralizing antibody levels that inhibit infection of reporter cells. Results will be reported in 90% inhibiting concentration (IC90).

